## Abstract

**Abstract:**

**Introduction:**

Video games have been linked to a range of positive and negative effects on the mental health of adolescents and young adults. However, to better understand how games affect the mental health of young people, their use and experiences must be situated in the sociocultural and personal life contexts of individuals. Drawing from a cultural-ecosocial approach, this study combines cross-sectional and digital phenotyping measures to examine the effects of video games on the mental health of youth.

**Methods and analysis:**

Participants will be young people aged 16–25 years from the community and living in the province of Quebec, Canada. An initial sample of 1000 youth will complete a cross-sectional survey online, including measures of socio-demographic context, gaming practices and experiences, streaming practices and experiences, as well as personality and well-being. Qualitative questions will explore personal views on games and mental health. A subsample of 100 participants will be selected for digital phenotyping, including daily surveys of well-being, gaming, streaming and social experiences, combined with passive mobile sensing (eg, geolocation). Analyses will include regression and mixed models for quantitative data, reflexive thematic analysis for qualitative data, and an integration of quantitative and qualitative results using participatory methods.

**Ethics and dissemination:**

The study received ethical approval from the Institutional Review Board of McGill University (24-02-015). The dissemination of results will be conducted in partnership with a multi-stakeholder advisory committee, including youth who play video games, and will involve peer-reviewed publications, presentations to policymakers in Quebec, and workshops for clinicians and researchers.

STRENGTHS AND LIMITATIONS OF THIS STUDYThe inclusion of structural factors, social affiliation through play and streaming-related experiences addresses gaps in the literature regarding the sociocultural influences of games on mental health.Digital phenotyping will allow for the robust examination of within-person dynamics that are independent from the confounding influences of unmeasured individual traits.The combination of quantitative and qualitative data will provide a more comprehensive and nuanced understanding of games and mental health.Convenience sampling in a specific region (the Quebec province in Canada) limits the generalisability of the results.Given the heterogeneity of game genres and social contexts surrounding game experiences, the study measures can only partially capture their diverse ramifications for mental health.

## Introduction

 Video games are highly popular among youth aged 16–25 years old.^1 2^ In the province of Quebec, Canada, the Entertainment Software Association of Canada reports that 71% of young adults own a video game console, and 41% of Quebecers (10% more than other Canadians) play games regularly.^3^ In Canada, the average video gaming time is 6.5 hours/week among female young adults and 10.2 hours/week among male young adults, in line with global trends.^4 5^ Some 82% of male and 58% of female players declare themselves to be ‘gamers’.^6^ For the 74% of Canadians who grew up playing video games, 74% are passing on the hobby, playing video games with their children as a way of spending time together.

Although video gaming has become a multigenerational activity, there is a long history of concerns about its potential negative impacts on the well-being of young people. Early studies have suggested that violent games increase the aggressivity of young players,^7^ or that excessive screen time might be at the expense of sleep, school, work, physical activity or interpersonal activities necessary for maintaining a person’s overall functioning and well-being.^8 9^ Screen time refers to the amount of time spent on electronic devices, such as video games, and is commonly perceived as a behaviour that can negatively influence physical and mental well-being.^10^ These putative effects of video games and screen time have become controversial owing to methodological and conceptual issues (a review of which is beyond the scope of this protocol), but they continue to animate scientific and popular discourses on video games.^11^

Another concern about games is that they may become the source of addictive behaviours. The International Classification of Diseases, 11th revision, recognised this addictive potential under the label of gaming disorder, defined as ‘impaired control over gaming, increasing priority given to gaming over other activities (…), and continuation or escalation of gaming despite the occurrence of negative consequences’.^12^ Critical perspectives on gaming disorder have highlighted the challenge of differentiating high engagement in video games that is not pathological from ‘truly’ addictive forms of gaming.^13 14^ Clinical research seeks to advance the detection and treatment of gaming disorder with the hope of improving youth mental health,^15^ and in this context, it has been suggested that high engagement in games might trigger or amplify psychotic symptoms in some individuals.^16^ However, developmental research into gaming and psychotic-like experiences suggests that the two may be linked through shared risk factors, such as challenging life circumstances, rather than a causal effect of gaming on psychosis.^17 18^

While concerns about problematic gaming have dominated clinical discourse, there is evidence for positive effects of video gaming, which may help explain why some people turn to video games to deal with challenging situations. Observational research using in-the-moment (ie, ambulatory) assessments and natural experiments has shown that people’s mood improves when they play video games,^19 20^ suggesting a role for video gaming as an emotion regulation strategy. The experience of immersing oneself in games may contribute to providing a relief from day-to-day stressors while providing an alternative environment to fulfil psychological needs (eg, of social connection).^21^ Surveys, laboratory experiments, qualitative interviews and ethnographic research support the importance of social connectedness enabled by video games for well-being.^22^,^25^ Moreover, games afford opportunities to embody virtual characters with desirable traits or elevated social status, conferring opportunities for young people to explore and adaptively experiment with their identity.^22 26^ Finally, some video games solicit cognitive functions in ways that may enhance processing, memory and multitasking skills over time.^27^

Beyond the immediate context of game play, shared interest in games serves as a scaffolding for communities of gamers who meet and socialise in a variety of spaces. Fan communities of video games may enrich the social capital of young players by offering opportunities to establish new relationships and make a living from streaming activities;^28^ however, they may also be places of exclusion, harassment and discrimination that hamper the well-being of their members.^29^ Streaming platforms such as Twitch are key spaces where people interact over a common interest in a game, a game performance and/or a content creator (the streamer).^30^ The culture of esports (competitive and/or professional game play) and streaming expands the range of experiences enabled by video games: through these game-related productions and events, people interested in video games can interact with like-minded peers (eg, by contributing to group discussions in streaming channels) and engage with the narratives and mechanics of play without being the player. Although the popularity of video game streaming has significantly increased over the last decade, the role of this phenomenon in the mental health of young gamers remains underexplored in research.

## Theoretical framework

The range of putative benefits and harms of video games for mental health is not surprising when we consider the diversity of games, the psychological features and personal histories of players, and the sociocultural contexts in which gamers and games are embedded.^31 32^ We posit that a cultural-ecosocial approach to mental health^33^ provides a helpful framework for examining the multifaceted connections between games and mental health. According to the cultural-ecosocial view, environmental influences on mental health can be disaggregated into at least four domains: (1) Lifespan developmental history, (2) Social structure and positioning, (3) Cultural meaning, norms, values and affordances and (4) Individual biography and self-understanding. This approach builds on previous biopsychosocial accounts of mental health by specifying the mechanisms that connect environment, culture and mental health^34^ and has been proposed as a framework for advancing neuroscience and precision psychiatry research.^35 36^

*Lifespan developmental history*. Lifespan development encompasses the psychological needs, social roles and unique psychological traits of individuals that shape the impacts of games on mental health. Granic^26^ argued that for adolescents and young adults, games offer rich opportunities to develop their identities, practise prosocial behaviours and form intimate bonds with their peers, which are central to this period of life. Self-determination theory advances that gaming can be motivated by the fulfilment of psychological needs for autonomy, competence and connectedness,^25^ and empirical evidence suggests a positive effect on the well-being of players who successively satisfy these needs through video games.^37^ However, excessive video gaming (ie, gaming disorder) may interfere with role fulfilment, including relationships with peers and family, as well as school functioning, for some individuals.^38^ Digital phenotyping, which involves ambulatory collection of active (eg, surveys) and passive (eg, geolocation) data, may provide indirect markers of gaming disorder;^39^ notably, greater time spent at home according to geolocation has been associated with depressive symptoms^40^ and could hypothetically index reduced mobility as a consequence of prolonged gaming sessions. Importantly, the practices and outcomes of video games vary in part as a function of the psychological propensities of players. For example, there is some evidence that the experience of being immersed in a video game (ie, the degree to which the person feels absorbed in the game^41^) is associated with improvements in emotional states,^42^ but immersion has also been hypothesised to contribute to the risk of gaming disorder.^43^ A better understanding of how individuals fulfil their developmental needs and self-determination through games, and how they differ in their propensity to experience immersion, could support a more personalised assessment of the risks and benefits of games.

*Social structure and positioning*. Social structures and the positioning of individuals can influence how and why they engage with games. In the face of social exclusion or challenging life circumstances, some people will turn to video games as a means of immersing themselves into a more welcoming environment and for making friends online.^21 24 44^ For individuals living in socioeconomic precarity, games may be a safer and more accessible activity relative to other pursuits, which could explain why lower household income or parental socioeconomic status are associated with higher levels of adolescent video gaming in some samples.^18 45^ Disability may increase the salience of gaming as an activity that is relatively more accessible than others to fulfil psychological needs for self-determination;^46 47^ however, disability may also limit the accessibility of games that solicit particular physical or cognitive resources. Women, queer and racialised gamers are at increased risk of exposure to harassment and discrimination in game communities and online multiplayer games.^48 49^ These examples illustrate how social structures and positioning can predispose to or interfere with a range of game-related experiences.

*Cultural meaning, norms, values and affordances*. The shared norms and values of a person’s social network may encourage or discourage certain ways of engaging with games. For one, being part of a group of friends who share one’s interest in games lends a particular meaning to games as something that fosters and nourishes friendships. Playing games jointly with friends or family affords an opportunity for social connection that contributes to individual well-being.^50^ In the absence of such social ties, there may be fewer opportunities to integrate in-game accomplishments and experiences outside of the game environment—and possibly increased risk of facing the disapproval of others for what is often deemed to be excessive ‘screen time’.^51^ Although the role of these cultural factors in the mental health effects of games remains underexplored, we can posit benefits (eg, social connectedness) and risks (eg, stigma and isolation) related therefrom. Positive and negative effects of games may thus be uncovered in research by considering the alignment or mismatch of gaming behaviours with norms and values in the person’s social environment.

*Individual biography and self-understanding*. Unique aspects of gaming experiences might influence the self-concept and well-being of individuals in ways that are not fully captured by existing theoretical frameworks. Focusing solely on theorised mechanisms of effects on mental health, such as gaming disorder or psychological need satisfaction, risks overlooking the unique ways in which games can bring pivotal life experiences for individuals.^26 52^ For this reason, exploring the lived experiences of young players in an open-ended fashion, for example, through qualitative and participatory methods, is essential for producing a comprehensive understanding of gaming and mental health.

## The present study

Research published to date has largely relied on cross-sectional samples, limiting the capacity to remove confounding influences from individual characteristics of participants. In addition, existing research infrequently accounts for streaming practices and the role of social factors in the associations between video games and mental health. As highlighted above, video games may have different impacts on mood and well-being depending on the person’s social context, the psychological mechanisms that are activated and the overall characteristics of video game habits and streaming activities. Given the potential influences of social context on these associations, it is necessary to consider features such as socio-economic status, gender, ethnoracial identity, (dis)ability, as well as game-related practices that are shared with friends or family.

This study will thus aim to investigate the associations of video game-related experiences with mental health in youth aged 16–25 years old from the general population of the province of Quebec, Canada. The study will have two components: a cross-sectional survey of 1000 individuals recruited by convenience in the community and including a mix of quantitative and qualitative items, followed by digital phenotyping (ie, daily diaries and mobile sensing) in a subsample of 100 individuals over 2 weeks. The key objectives of the study, listed in table 1, focus on psychological needs, immersion, game-related social affiliation, harassment and discrimination, and self-narratives about games and mental health. A distinctive feature here is the inclusion of psychotic-like experiences, which are rarely investigated in the field of games and media effects but are considered a transdiagnostic marker of risk for mental health problems during adolescence and early adulthood.^53^ Additional objectives will be to examine the associations of streaming-related experiences with well-being, and to explore the predictive utility of mobile sensing data (eg, geolocation). This study follows the Strengthening the Reporting of Observational Studies in Epidemiology reporting guideline.^54^
Figure 1 summarises the study design and theoretical framework.

**Table 1 T1:** Main objectives of the study and related variables

Predictors	Outcomes	Framework domains
*Objective 1. To examine whether the satisfaction of psychological needs and social affiliation through games is associated with well-being* Hypothesis: Greater play time with others, higher scores for belonging and need satisfaction, and lower scores for need frustration will be associated with lower levels of psychotic-like experiences and higher levels of well-being		
Play time with others (C) Fandom Functions Scale—Belonging (C) Basic Needs in Games Scale, gaming and streaming (L)	Psychotic-like experiences (C) Daily well-being questionnaire (L)	Lifespan developmental history; Cultural meaning, norms, values and affordances
*Objective 2. To examine whether a greater propensity for immersion is associated with better satisfaction of psychological needs and improved well-being through games* Hypothesis: Higher scores for absorption and daily immersion will be associated with higher levels of fandom functions, need satisfaction and daily well-being, but also higher levels of psychotic-like experiences and problematic gaming		
Tellegen Absorption Scale (C) Daily immersion (L)	Fandom Functions Scale (C) Basic Needs in Games cale, gaming and streaming (L) Daily well-being (L) Psychotic-like experiences (C) Problematic gaming (C)	Lifespan developmental history
*Objective 3. To examine the associations of marginalised identities with exposure to harassment and discrimination in games or streaming, and the mediated associations with well-being* Hypothesis: Participants identifying as female, transgender or non-binary, from an ethnoracial minority, or having a history of mental health problems will report higher levels of exposure to bullying, which will mediate an association with lower levels of daily well-being		
Sex and gender (C) (Dis)ability (C) Racialised identity (C) History of mental health problems (C)	*Mediator:* Exposure to bullying (C, L) Daily well-being (L)	Social structures and positioning
*Objective 4. To explore young people’s narratives about the role of games and streaming in their lives and their mental health* This exploratory objective has no hypothesis and will rely on qualitative data from open-ended questions (C)		
N/A	N/A	Individual biography and self-understanding

C, cross-sectional sample (n=1000); L, longitudinal, digital phenotyping subsample (n=100).

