### Rationale for the sample size

Given the variety of objectives and analyses planned, we established the sample size based on two basic scenarios: a linear regression of one cross-sectional variable over another (n=1000) and a generalised linear mixed model where one daily digital phenotyping variable is regressed over another (n=100). For the cross-sectional scenario, we conducted the power analyses in G*Power, V.3.1.9.7. We calculated that a sample of n=1000 will be sufficient to detect a linear regression slope of β=0.09, assuming a type I error rate of 0.05 (two-tailed) and statistical power of 85%. This would be sufficient to evaluate, for example, a weak but significant association between greater belonging and lower levels of psychotic-like experiences (Objective 1) or a greater propensity for immersion and greater psychological functions of games (Objective 2). For the digital phenotyping component, we used the sample size calculator developed by Barnett and colleagues:^56^
https://onnela-lab.shinyapps.io/digital_phenotyping_sample_size_calculator/. We found that a sample size of 100 persons with daily measures over 2 weeks will provide statistical power of 93% to detect effect sizes of β=0.07 with a type I error rate of 0.05, assuming 50% missing data and random-effect variance of 1.1. These parameters would be sufficient to examine the association between daily needs satisfaction in games and daily well-being (Objective 1) or the association between daily immersion and daily well-being (Objective 2). This statistical power estimation also applies to passive sensor data (eg, geolocation) transformed into daily features (eg, daily time spent at home).

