### Analyses

We will conduct quantitative analyses in R (R Foundation for Statistical Computing). Characteristics of the analytic samples (cross-sectional and longitudinal) will be described to identify the potential underrepresentation of groups (eg, gender, ethnoracial, socioeconomic or rural vs urban groups) that may limit the generalisability of findings. Using lavaan,^84^ we will examine the factor structure and internal consistency of ad-hoc or modified questionnaires, and, for analyses of longitudinal changes over time, we will also test for longitudinal measurement invariance.^85^ Statistical significance will be defined as p<0.05 or 95% CIs not overlapping the null. We will apply correction for false discovery rate using the Benjamini and Hochberg^86^ method when multiple predictors are tested for a single hypothesised outcome (eg, there are two predictors of psychotic-like experiences for Objective 1: play time with family, friends or romantic partners, and the modified Fandom Functions Scale—Belonging). We will analyse cross-sectional outcomes using generalised linear models adjusted for relevant socio-demographic characteristics (eg, sex, educational attainment and occupational status). In these models, missing data will be handled by complete case analysis or multiple imputation. We will analyse longitudinal outcomes (eg, daily well-being) using generalised linear mixed models with observations nested in individuals. Missing data will be handled by maximum likelihood. To parse out within-person and between-person associations between longitudinal repeated measures (eg, the association between daily psychological need satisfaction and daily well-being), we will apply person-centring and mean-centring to the predictors; this approach accounts for time-invariant, unmeasured individual factors that could confound associations between the predictor and outcome.^55^ Mobile sensing data will be transformed into higher-level, validated features over epochs of 1 day for integration into generalised linear mixed models as exploratory predictors of game-related experiences and well-being; for example, geolocation data will be used to infer the daily amount of time spent at home.

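### If Objective 2 is right, leaving absorption out of the Objective 1 model shifts the Belonging slope on psychotic-like experiences upwards and may mask the hypothesised negative association

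*Protocol article*

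**What the plan says.** In Table 1 (The present study), Objective 2 takes the Tellegen Absorption Scale as a predictor. It lists the Fandom Functions Scale and psychotic-like experiences among the outcomes, all from the cross-sectional sample. The hypothesised signs are positive for both. On the fandom scale the table reads: "Higher scores for absorption and daily immersion will be associated with higher levels of fandom functions, need satisfaction and daily well-being". On psychotic-like experiences, the same hypothesis adds: "but also higher levels of psychotic-like experiences and problematic gaming". Cross-sectional measures describes Belonging as one of that scale's three subscales, beside purpose and escape.

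Objective 1 takes Belonging as a predictor and states that higher scores "will be associated with lower levels of psychotic-like experiences and higher levels of well-being".

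Analyses says that cross-sectional outcomes are modelled with generalised linear models "adjusted for relevant socio-demographic characteristics (eg, sex, educational attainment and occupational status"). It names two Objective 1 predictors of psychotic-like experiences: play time with others and Belonging. Absorption is listed under Personality in Cross-sectional measures, so it lies outside the stated class of covariates.

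Rationale for the sample size is built on "a linear regression of one cross-sectional variable over another (n=1000") and states that a "sample of n=1000 will be sufficient to detect a linear regression slope of β=0.09". Its first example is "a weak but significant association between greater belonging and lower levels of psychotic-like experiences (Objective 1").

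**The concern.** The protocol's own hypotheses tie absorption, with the same sign, to both sides of an association that Objective 1 expects to be negative. The Theoretical framework also treats players' psychological dispositions as partly shaping their gaming practices and what follows from them, which puts a trait such as absorption upstream. A variable with positive links to predictor and outcome pushes the slope between them upwards when it is left out.

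The target slope is only 0.09, so modest links are enough to matter. The person-centring described in Analyses does not help here: it removes stable traits for predictors measured daily, whereas Belonging and psychotic-like experiences are each measured once. A null Belonging result from the stated model could therefore reflect either no association or one masked by absorption, and the model alone would not tell them apart.

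**Working it through.** **Inputs from the protocol.** n = 1000, two-sided alpha 0.05, power 85%, slope 0.09, one predictor (Rationale for the sample size). Signs: absorption–fandom functions positive, absorption–psychotic-like experiences positive, Belonging–psychotic-like experiences negative (Table 1).

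**Assumed inputs.** All variables have unit SD. Let a be the absorption–Belonging correlation, c the slope of psychotic-like experiences on absorption with Belonging held fixed, and b the Belonging slope with absorption held fixed. The documents give neither a nor c; 0.1 to 0.3 is used for each. Socio-demographic covariates and the false discovery rate correction are ignored, as in the protocol's own calculation.

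**Step 1: the stated figure.** Power comes from the noncentral t with 998 df and ncp = |β|√n / √(1 − β²). Solving for 85% power gives β = 0.0944, which rounds to the stated 0.09. At exactly 0.09, ncp = 0.09 × 31.62 / 0.996 = 2.86 and power is 81.5%. That is the reference value below.

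**Step 2: direction.** Slope without absorption = b + a·c. Objective 2 concerns the absorption–outcome correlation r = c + a·b, so c = r − a·b. With a > 0, r > 0 and b < 0, c exceeds r and is positive, so the added term a·c is positive.

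**Step 3: reading A, absorption-adjusted slope b = -0.09.** With absorption in the model, SE = √[(1 − R²) / (n(1 − a²))] and R² = b² + c² + 2abc. For a = c = 0.3, R² = 0.0081 + 0.09 − 0.0162 = 0.0819, SE = √(0.9181/910) = 0.0318, and power is 80.9%.

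| a = c | a·c | Slope without absorption | Power without | Power with |
|---|---|---|---|---|
| 0.1 | 0.01 | -0.08 | 72% | 81.5% |
| 0.2 | 0.04 | -0.05 | 35% | 81.3% |
| 0.3 | 0.09 | 0.00 | 5% | 80.9% |

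A simulation of 4000 runs at a = c = 0.3 rejected in 4.9% of runs without absorption. Fixing the correlation r instead of c changes little: slopes of -0.079, -0.046 and +0.008, with power of 71%, 31% and 6%.

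**Step 4: reading B, crude slope = -0.09.** The unadjusted test keeps its 81.5%. The absorption-adjusted slope is (-0.09 − a·r) / (1 − a²):

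- a = r = 0.1: -0.10/0.99 = -0.101
- a = r = 0.2: -0.13/0.96 = -0.135
- a = r = 0.3: -0.18/0.91 = -0.198

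**Step 5: can all the hypotheses hold at once?** For correlations 0.3, 0.3 and -0.09 the determinant is 1 − 0.09 − 0.09 − 0.0081 + 2 × 0.3 × 0.3 × (-0.09) = 0.796. It is positive, so the correlation matrix is valid and they can.

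**The case against.** A reader might infer that Objectives 1 and 2 contradict each other, or that Objective 2 implies a positive Belonging–psychotic-like experiences correlation. Neither follows: Step 5 shows that all the hypothesised signs can hold together without conditioning on anything.

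A reader might also infer that the planned test is underpowered as written. The sample-size section powers a regression on one predictor, so its 0.09 is most naturally a crude slope. Under that reading (Step 4) the test loses no power, and the losses in Step 3 appear only if 0.09 is taken as the absorption-adjusted slope. This objection stands, and it is why both readings are shown.

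Other points on that side carry weight:

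- The path sizes are assumptions. At 0.1 each, the loss is about 10 percentage points of power.
- Objective 2 speaks of associations and names the whole Fandom Functions Scale. The link could run mainly through purpose or escape, and calling absorption a common cause is an inference.
- Objective 1 is itself worded as an association, so a null crude slope would still count against it as worded.
- Big Five traits, social support and mental health history are also collected and could confound the same slope, some in the opposite direction.
- The listed covariates are examples, and a full list may sit in an analysis plan that is not shown. The class named is nonetheless socio-demographic, and a personality trait is not in it.

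None of this changes the direction of the shift if Objective 2 holds for Belonging.

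**Conclusion.** The point holds as a conditional one. If absorption is positively associated with both Belonging and psychotic-like experiences, as Objective 2 predicts for the parent scale, the Objective 1 slope without absorption lies above the absorption-adjusted slope. For paths of 0.1 to 0.3 the shift is 0.01 to 0.09, against a target of 0.09. The consequence is either reduced power for an absorption-adjusted slope of -0.09, or an understated absorption-adjusted slope if the crude value is -0.09. A negative crude slope remains possible in both cases.

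The size rests entirely on assumed paths, and treating the shift as confounding bias rests on absorption being upstream. The documents support neither a contradiction between the objectives nor a demonstrated power shortfall in the plan.

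For Belonging and daily well-being, in the subsample of 100, the same omission would act in favour of the hypothesis. Its size was not calculated.

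**What to change.** In Analyses, add the Tellegen Absorption Scale score as a covariate in the cross-sectional Objective 1 Belonging model for psychotic-like experiences. Report the Belonging slope with and without it, and note that other traits may still confound. The same pair of models may be reported for Belonging and daily well-being.

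The cost is one line of text and no new data, because the scale is already part of the cross-sectional survey. The downsides are a slightly wider interval if absorption and Belonging are strongly correlated, and some residual confounding from other traits.
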